#### Facilitator support

During the intervention, the participants will be supported by an assigned healthcare professional, who will act as their facilitator. Facilitators will be recruited (and trained) from our 15–20 sites, aiming for at least 2 per site, enhancing generalisability. Facilitators will predominantly include IBD nurses and a small number of academic psychologists within the research team in instances where nurses are not available, for instance supporting participants recruited through non-hospital sites.

The programme suggests one 30-min phone call after participants have completed session 1, and then online messaging from the participant to the facilitator as the participant wishes thereafter. During the phone call, the facilitator will review the participant’s personal vicious cycle completed in session 1, guide the participant’s understanding of factors contributing to symptoms from a cognitive behavioural model and review the participant’s programme aims. Each facilitator will use a telephone checklist prompt sheet to guide the telephone call. At the end of each online session, the participant is prompted to consider if they want to send a message. The facilitator can reply to online messaging within the intervention platform. The facilitator will have access to information on how participants are using the intervention (sessions and task completed) and will monitor and help to promote participants’ engagement with the intervention, together with supporting participants work toward achievement of their intervention goals. Facilitators will be encouraged to log in weekly to check their participant’s completion of sessions/tasks and send any necessary messages to promote engagement, as well as reply to messages received.
*Group 1 (intervention)*: Access to care as usual plus the online tailored BOOST self-management programme for 6 months, plus one individual telephone or Skype support session (for up to 30 min, training and a paper copy of the content will be provided for the facilitator), plus access to online messaging with their facilitator via the BOOST platform for the first 3 months after recruitment.

Participants will log in to the online programme (unique login), undertake symptom self-assessment, prioritise what symptom they want to work on, with signposting to relevant sections depending on symptoms and response to online questions. (Example: link to a section on improving sleep patterns for those with fatigue who nap a lot in the day or with a problem getting to sleep at night).
*Group 2 (control)*: Care as usual (CAU).

All participants will have access to all usual IBD care, including monitoring with clinic visits and/or via the local IBD helpline (this will constitute care as usual for group 2).

Participants in group 1 with an active IBD flare during intervention will not be expected to discontinue the intervention and will have continued access to the online programme. All randomised participants, regardless of whether they have reported a disease flare or not, will be sent the questionnaires to capture outcome measures at 6 and 12 months after randomisation.

At 12 months, participants allocated to CAU will be offered access to the online intervention (but no facilitator support). Uptake within 6 months will be reported.

For use of primary and secondary healthcare, other health care resources and medication use will be collected using the baseline, 6- and 12-month follow-up questionnaires (see Economic Evaluation section below).

We have worked with our patient panel to devise strategies to optimise engagement with the online intervention and retention of our sample, such as personalised text or email reminders.

#### Facilitator training and intervention fidelity

There will be specific training for facilitators on delivering the intervention and the principles of CBT via a manual (which contains the full text of the online intervention for reference) and a 1-day intensive course delivered by expert psychologists in the intervention development team. The training will introduce facilitators to the principles of a cognitive behavioural approach, provide opportunity to observe and practice telephone call role plays and review example models of vicious cycles of symptoms which participants will construct during session 1. The training will also cover responding to online messaging, and what to do in certain situations (e.g. the participant not engaging with the programme, getting stuck or frequent or persistent use of the messaging service). Adverse events will be discussed and the manual contains standard operating procedures (SOPs) for actions to be taken in certain scenarios, such as the participant appearing very depressed or suicidal.

Facilitators will receive further training and supervision during the site initiation visit from the intervention development/trial team. Prior to starting the trial, facilitators will also receive one-to-one supervision on a ‘practice patient’ (a person with IBD from our Patient and Public Involvement panel) over a 2-week period. A practice telephone session between facilitator and patient will be audio-recorded for training purposes, where facilitators will use the telephone checklist prompt sheet to guide the call. Facilitators will receive feedback from a member of the intervention development team on the telephone conversation and online messaging responses with the practice patient.

Online messaging contacts will be recorded and analysed in the process evaluation (below). Facilitators will receive monthly supervision (or on request of the facilitator) with a trained member of the research team to ensure fidelity and provide support for any difficult issues that may arise. Supervision will include reviewing online messaging and tasks. Participants are told when they commence the online programme that their facilitator and the supervisor will be able to see their messages and tasks. Facilitators will complete the telephone checklist prompt sheet for each participant and provide these to the research team, and receive supervision on a trial patient telephone call, upon the patient’s permission for a psychologist to listen (but not audio record). At the end of the trial, a randomly selected sample of online messages will be rated for fidelity by an independent rater (see process evaluation below).

#### Discontinuation criteria

We do not have any criteria for discontinuing a participant.

### Outcomes

Trial outcome measures have been selected following focus group opinions and refined with our patient panel.

### Primary outcome measures

UK Inflammatory Bowel Disease Questionnaire (UK-IBDQ) [47] and global rating of symptom relief at 6 months after randomisation.

### Other measures (at baseline, and as secondary outcomes at 6 and 12 months after randomisation)

UK-IBDQ [47] at 12 monthsRating of satisfaction with results of IBD-BOOST programme (simple 0–100 visual analogue scale) at 6 and 12 months onlyGlobal rating of symptom relief at 12 monthsNumerical (0–10) pain rating scaleVaizey (faecal) incontinence score [48], reflecting patients’ perceptions of severity [49]IBD-Fatigue score [50, 51]IBD-Control score; 8-item self-reported score to measure disease control from the patient’s perspective [40]EQ-5D-5L [52] general health-related quality of life at baseline and 6 and 12 months after randomisation

### Health economic measure (at baseline, and 6 and 12 months after randomisation)

IBD Resource Use Questionnaire to determine health care and other resource use and costs due to IBD, including visits or phone calls to primary and secondary healthcare services, medication use and personal expenses.

### Moderators and mediators

These include measures which may either moderate or mediate the treatment response. These data are important in terms of variables which may help to explain response, to be used as part of process evaluation (see below): (at baseline, 6 and 12 months after randomisation):
Symptoms which determine a co-diagnosis of irritable bowel syndrome (IBS) and IBD: Rome IV criteria for IBSMedications for depression, pain and diarrhoeaMeasures of change in general mood: depression as measured by the Patient Health Questionnaire (PHQ-9) [53]. This measure includes a question (item 9) that may indicate suicidal thoughts. The action to be taken if suicidal thoughts are indicated is described in ‘Assessment and management of risk’ below.To measure self-efficacy: Self-efficacy for managing chronic disease 6-item scale [54]To measure IBD/illness specific cognitions: Brief Illness Perceptions Questionnaire (BIPQ) [55] (minus the open ended causal items). Items are prefaced in relation to beliefs about IBD symptoms rather than IBD generally.Medications for depression, pain, diarrhoeaTo measure IBD/illness specific affect: Visceral Sensitivity Index (VSI): gastrointestinal symptom-specific anxiety [56]To measure behaviour: All-or-nothing and avoidance/resting subscales from the Cognitive and Behavioural Responses to Symptoms Questionnaire (CBRQ)

Note: these outcome sets are questionnaires validated for self-completion and will be compiled into a single online questionnaire (available from the Chief Investigator). We recognise the potential burden on participants of these multiple outcome measures (just under 150 questions). However, as we are assessing multiple symptoms and are keen to include potentially explanatory variables, we feel that these are necessary. We have worked with our PPI representatives on optimising format for outcome measures in a user-friendly online interface.

#### Participant timeline

This is shown in Table 3. There are no face-to-face visits; all study procedures are completed remotely by post, telephone or online messages.

**Table 3 Tab3:** IBD-BOOST RCT screening and data collection schedule (SPIRIT figure)

	*Pre-consent*	*Pre-baseline*	*Baseline*	*6 months*	*12 months*	*Ongoing or during treatment*
Screen for eligibility	X					
Study within a trial (SWAT) randomisation	X					
Invite reply	X					
Consent form		X				
Red flags assessment		X				
Adverse event form						X
Drop-out event form						X
Faecal calprotectin test		X				
Baseline case report form			X			
Follow-up case report form				X	X	
Participant qualitative interviews			X		X	
Clinician qualitative interviews			X		X	
Randomisation			X			
Nurse support				X		
Intervention website user query				X		

#### Sample size

Our primary outcome is the UK-IBDQ, range 0 to 120 where low values indicate poor quality of life. Using several published studies [47, 57, 58], we estimate the standard deviation of the change in score to be between 20 and 30. This would mean an effect size of 0.3 would equate to a difference of between 6 and 9 points on the scale. In the validation study [47], the difference in score between those with mild disease and disease in remission was 12 points and the effect of relapse was 10 points.

An effect size of 0.3 was observed in a small study of dietary advice in patients with ulcerative colitis [57].

We will randomise 680 patients, 340 in each group. Assuming a 20% loss to follow-up, there will be 270 in each group in the analysis. Assuming there are 30 facilitators, they will each support ~ 11 patients on average of whom ~ 9 will contribute to the analysis. If the ICC for clustering between facilitator is 0.04, the design effect will be 1 + 0.04 × 8 = 1.32 and the effective sample size in the intervention arm is 270/1.32 = 204. 270 in the control and 204 in the intervention arm would allow an effect size of 0.3 to be detected with 90% power.

A 20% drop-out assumption is based on drop-out rates from previous studies of self-management: 19.2% of 682 participants in IBD disease self-management (not online) [59]; 20.4% of 333 participants for online self-management of ulcerative colitis disease flares [33]; 18% control and 16% intervention of 1140 participants randomised for chronic disease self-management in other diseases [37].

#### Recruitment

The previous stage of our programme involves a large-scale survey about symptoms to people with IBD. We will continue sending out batches of this survey until we achieve adequate recruitment for the RCT. Respondents to this separate survey who are apparently eligible to participate in the RCT will be sent an invitation, a participant information sheet, a consent form and a further pre-randomisation eligibility checklist for ‘red flags’ (see eligibility criteria above) electronically or by post. Once a patient has consented and is eligible, a baseline questionnaire is sent.

## Methods: assignment of interventions

### Randomisation procedures

Participants who consent, are eligible and return the baseline questionnaire (which is different form the survey they will have already completed) will be randomised by the central research team using an online randomisation system developed for the study by the PCTU. Allocation will, therefore, be concealed until consent and baseline measurements have been completed. It is not possible to blind participants or facilitators once randomisation has occurred, due to the nature of the intervention.

The central team will inform the participant which group they are in and inform the clinical sites of participants in group 1 who will receive local facilitator support (phone call and online messaging). The local facilitator will be given the participant’s details and access to their online tasks.

Stratified central web-based randomisation to 2 groups. Stratified by:
Diagnosis (Crohn’s disease vs. any other type of IBD, including ulcerative colitis and IBD-unclassified)Whether or not participated in the stage 3 study in this programme (medical symptom optimisation)

Random block sizes of 4 and 6 will be used. Block sizes will not be disclosed to ensure allocation concealment.

### Blinding procedures

Faecal calprotectin level will be entered into the database by a person blinded to group allocation when the result has been returned from the laboratory and the participant informed of the result. Blinding of participants or facilitators is impossible. Data cleaning for the outcome measures will be by a statistician blinded to group allocation. Blinding beyond this will be impossible as data is clustered by the facilitator in the intervention arm only.

## Methods: data collection, management and analysis

### Data collection methods

Outcome measures will be collected by either direct participant input into a secure online study-developed database managed by the QMUL Pragmatic Clinical Trials Unit (PCTU) or via paper copies sent by central research team at KCL. Paper copies received in the post will be inputted manually into the database by the research team at KCL. The questionnaires will not be available in any languages other than English. Each clinic or site will complete a study log for all their participants who have been contacted for the study. Two email or text reminders will be sent to non-responders. If there is still no response, an attempt will be made to collect the primary outcome measure by telephone.

Window for return of outcome measures is as follows: up to 8 weeks (with reminders) at the 6-month follow-up and up to 4 weeks (with reminders) at the 12-month follow-up (with up to 2 text or email reminders). If primary outcome measure is not returned by 8 weeks after the 6-month time point, an attempt will be made to have this (the IBDQ and global rating of symptom relief only) completed over the phone by a member of the central trial team reading out the questions and recording the responses.

Baseline demographic details (age, gender, type of IBD) and ROME IV criteria for irritable bowel syndrome [60] will be collected.

We will adopt evidence-based methods to minimise loss to follow-up which have been identified in a systematic review [61]. These include providing incentives to participants, contacting respondents prior to sending the follow-up questionnaires and using phone, text and email to contact participants. To optimise our response rates, we will provide an unconditional inconvenience payment of £5 at 6 months and 12 months by post with a letter at the same time as we send out the follow-up questionnaire electronically or by post.

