### Qualitative

Fidelity to the intended facilitator support: a sub-set of facilitators’ messages will be analysed and compared with instructions in the training manual for fidelity to the intended facilitator support. All facilitator interactions online with participants will be captured and randomly selected interactions (messaging) will be stripped of all personal identifying data and subjected to content analysis [65], to enable assessment of intervention fidelity (as defined by the training day and intervention manual).Face-to-face, telephone or Skype interviews with a purposive sample of up to 30 recruits (or until apparent data saturation) before and after the intervention (attempting to recruit the same people before they know their group allocation and then the same people 6 months later; if it is not possible to recruit people for a second interview at 6 months (or when they drop out if this is sooner), these participants will be replaced by another participant who was allocated to the same group with broadly the same characteristics). Interviews will be completed at different times after recruitment, to understand expectations and experiences of the intervention, its acceptability and which aspects they felt were most or least helpful (informing adjustment to the intervention before future rollout), and for their opinions on changes in their cognitions and behaviours. We will also interview at least two thirds of the facilitators who are IBD nurse specialists (approx. 20: or until apparent data saturation) to understand their views on supporting the online intervention and fit with their existing workload.

Participants who have indicated on the trial consent form that they are happy to be approached about interviews will be purposively selected and consented for interviews. Facilitators indicating willingness will be interviewed. The topic guides for interviews have been developed with our PPI panel. Data will be analysed iteratively and as the interviews progress the topic guide will be adapted, based on themes which emerge from earlier interviews, to enable exploration of issues which appear relevant in later interviews.

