### Harms

#### Assessment and management of risk

This is a low-risk study (as assessed by PCTU), although there is potential for participants to become distressed when thinking about their symptoms. The intervention site will include a link / website address to CCUK who provide support via their helpline, and contact details are included in the Participant Information Leaflet. The outcome measures include questions on anxiety and depression and the PHQ-9. The central research team will monitor responses to suicidal thoughts and contact the patient and undertake a risk assessment if necessary. At the end of the questionnaire, there are helplines listed that can offer support.

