#### Adverse events (AEs)

Adverse events will be assessed using the follow-up questionnaire at the 6- and 12-month follow-up and may also be recorded by facilitators through communication with participants in the intervention arm. We will also attempt to capture any unforeseen consequences in the qualitative interviews.

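### The 6-month telephone follow-up of non-responders leaves out adverse events, so some 6-month harms information is avoidably lost at that contact

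*Protocol article*

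**What the plan says.** Under Data collection methods, the trigger for the call is "If primary outcome measure is not returned by 8 weeks after the 6-month time point". In that case "an attempt will be made to have this (the IBDQ and global rating of symptom relief only) completed over the phone".

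Under Adverse events (AEs), the main route for harms is the questionnaire: "Adverse events will be assessed using the follow-up questionnaire at the 6- and 12-month follow-up". Two further routes follow. Events "may also be recorded by facilitators through communication with participants in the intervention arm", and "We will also attempt to capture any unforeseen consequences in the qualitative interviews". The Qualitative section describes those as "interviews with a purposive sample of up to 30 recruits (or until apparent data saturation) before and after the intervention".

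Three other places bear on the point:
- The Facilitator support section says that all randomised participants, with or without a flare, "will be sent the questionnaires to capture outcome measures at 6 and 12 months after randomisation". It limits online messaging with the facilitator to the first 3 months.
- Table 3 lists an adverse event form as ongoing or during treatment. Expected events says that blank forms go to recruiting sites, that the investigator follows up serious events, and that elective and flare-related admissions are not collected or reported as serious adverse events.
- Assessment and management of risk relies on questionnaire answers for suicidal thoughts: "The central research team will monitor responses to suicidal thoughts and contact the patient and undertake a risk assessment if necessary".

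**The concern.** The people telephoned are those who did not return the form that carries the adverse event enquiry. The trial goes to the trouble of speaking to them, about 8 months after randomisation, under a rule that limits the conversation to the two primary outcomes. This is a stated choice and not a detail left to a fuller document.

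Two things are at stake. First, the 6-month primary outcome and the 6-month adverse event data will come from different sets of people, and a reader of the results could assume they are the same set. Second, an unreturned form costs more safety information under care as usual, where no facilitator is in contact, than in the intervention arm. There is no Data Monitoring Committee, so questionnaire data carry much of the harms evidence.

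**Working it through.** **The plan's own figures.** The article gives no figure for the number reached by telephone. Its one design calculation is unaffected by this point and reproduces: design effect 1 + 0.04 × 8 = 1.32; 270 / 1.32 = 204.5; power for an effect size of 0.3 with 270 and 204 participants is 0.899 against the stated 90%. This takes a two-sided 5% level, which is my assumption.

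**Routes for adverse events in someone reached only by telephone at 6 months.**

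| Route | Intervention | Care as usual |
|---|---|---|
| 6-month questionnaire | not returned | not returned |
| 6-month telephone call | two primary outcomes only | two primary outcomes only |
| Facilitator record | optional; messaging ends at 3 months | none |
| Ongoing adverse event form | no scheduled enquiry described | no scheduled enquiry described |
| Qualitative interview | up to 30 recruits across the trial | same pool |
| 12-month questionnaire | sent to all; recall period not stated | sent to all; recall period not stated |

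Under care as usual, nothing scheduled for every participant asks about adverse events between the unreturned 6-month form and the 12-month form. Whether the 12-month form recovers events from months 0 to 6 depends on a recall period that the article does not give. PHQ-9 item 9 sits in the same unreturned questionnaire and is likewise absent from the call.

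**How many people.** Randomised: 680 (Sample size). Share reached only by telephone: assumed 5% to 15%.
- 0.05 × 680 = 34
- 0.10 × 680 = 68
- 0.15 × 680 = 102

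These are separate from the 20% loss in the sample size section (0.20 × 680 = 136). Those people give no primary outcome at all, and adding questions to the call would not reach them.

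**How far a risk could be understated.** Let p be the event risk in those who return the questionnaire, f the share of telephone-only participants among all those reached, and k the ratio of their risk to p.
- True risk among those reached: (1 − f)p + f·k·p
- Risk seen from questionnaires: p
- Understatement: f(k − 1)p

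With p = 10% (assumed):

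| f | k = 1 | k = 2 | k = 3 |
|---|---|---|---|
| 5% | 0 | 0.5 points | 1 point |
| 10% | 0 | 1 point | 2 points |
| 20% | 0 | 2 points | 4 points |

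The whole effect comes from k. With equal risk there is no bias, only less information. The documents supply neither p, f nor k.

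**The case against.** A short call is a defensible choice. The full set runs to just under 150 questions, the article acknowledges the burden, the trial is rated low-risk, and completing the primary outcome comes first. The restriction also sits in a paragraph about return of outcome measures, so it may not have been meant to address event reporting. This explains the rule, but a few items asked after both primary outcomes would not endanger them, and nothing elsewhere adds an adverse event question to the call.

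Four stronger readings are tempting, and the documents do not support them.

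- *These participants are never asked about adverse events.* They are sent the 12-month questionnaire like everyone else, and that questionnaire also assesses adverse events. The ongoing form and the site forms may pick up some events too.
- *Harms are missing selectively, so counts will be too low.* It is plausible that illness or low mood leads to non-return, but the article does not establish it. Flare-related admissions, a likely link between illness and non-return, are in any case not collected or reported as serious adverse events.
- *A difference between arms in the share telephoned biases the harms comparison.* The gap arises from non-return. A person who has not returned the form lacks a 6-month answer whether or not they are telephoned; the call is a missed chance to recover it. The article also specifies no formal between-arm analysis of harms.
- *The questionnaire's adverse event items ask about hospital admission since randomisation.* The items are not reproduced, so their content and recall period are unknown.

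**Conclusion.** The point holds in a limited form. By a stated rule, participants reached only by telephone at 6 months are not asked about adverse events at that contact, and the remaining routes are partial and thinner under care as usual. On an assumed 5% to 15%, 34 to 102 of 680 people would have 6-month primary outcomes without 6-month questionnaire adverse event data.

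The loss of information is avoidable and may be unequal by arm. Any understatement of event risk depends on telephone-only participants having a different risk from those who return the form, which the documents do not show; with equal risk it is zero. The primary analysis and its power are untouched. This is an inexpensive improvement to safety ascertainment, not a threat to the trial's main conclusion.

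**What to change.** In Data collection methods, remove the word *only* from the description of the 6-month call. Add the follow-up questionnaire's existing adverse event items, worded as they stand, at the end of the call. Ask them after both primary outcomes, so that they cannot influence those answers, and identically in both arms. Handle the answers consistently with the Expected events section. Report the number of participants with 6-month adverse event data by arm and by mode of contact (questionnaire or telephone).

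The cost is a script change and perhaps a minute or two on a call already being made, plus making sure that callers can complete the existing adverse event form. The downside is a slightly longer call. The change does not reach people who cannot be contacted at all. It does not alter the handling of suicidal-thought monitoring, which is a clinical matter for the trial team. The denominators can be reported even for calls already made.
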